## Methods/design

An RCT design will be used to compare a waiting-list control group with an intervention group. Self-reported data will be collected pre-intervention (T_0_) and at 8-week (T_1_) and 16-week follow up (T_2_). The 16-week follow-up assessment serves as a primary endpoint to compare group effects. After the initial 16-week study period, the participants in the waiting-list control group can start using the Inlife platform, whereas caregivers in the intervention group are free to continue using the platform. Furthermore, a long-term follow-up measurement is scheduled for 42 weeks (T_3_) after baseline. See Fig. 1 for the flow diagram. This paper follows the Standard Protocol Items: Recommendations for Interventional Trials (SPIRIT) guidelines, which can be found in Additional file 1.

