### Sample size

The sample size was determined based on previous intervention studies of caregivers of PwD with the Short Sense of Competence Questionnaire (SSCQ) as an outcome measure [16, 36], using repeated measures and interaction within and between variables with a mean effect size of 0.5. In accordance with the following assumptions: alpha 0.05 and power 80%, we aim to include 102 primary caregivers (51 participants per group). Allowing for a 20% loss to follow up, we aim to enrol 122 caregivers.

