### Statistical analysis

#### Primary and secondary outcome measures

All analyses will be performed according to the intention-to-treat principle, using IBM SPSS Statistics (IBM Corp. Released 2016. IBM SPSS Statistics for Macintosh, Version 24.0. Armonk, NY: IBM Corp).

Prior to the main analysis, data will be examined for missing values, outliers and normality. To investigate whether randomisation was successful, potential differences in the baseline characteristics of the intervention and control groups will be determined using either the *t* test for the continuous variables or the chi squared (X^2^) test for the categorical variables. In the case of missing values, we will examine whether they are missing completely at random (MCAR). If the variables are MCAR, based on a comparison between the baseline characteristics of the study completers and the participants with missing values (no *P* value < .05), list-wise deletion will be applied, whereas when the missing values are not at random, we will apply a multiple imputation strategy [37].

To test the first hypothesis examining the differences in the outcome variables of the intervention group and waiting-list control group, analysis of covariance (ANCOVA) will be performed, with the outcomes of the T_2_ assessment (i.e., measured at 16 weeks, after this period the waiting-list control group can start with Inlife). The outcomes assessed at the T_2_ follow up will be included in the model as dependent variables and groups as between-subject variables. Potential baseline differences between the treatment arms will be included as covariates, if necessary. Each outcome measured will be assessed as a dependent variable in separate analyses.

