To test the changes in the primary and secondary outcome measures over the total study period, data from the intervention group and waiting-list control group will be analysed using a linear mixed model (LMM). The LMM will estimate the fixed effects of the regression slopes representing the changes during the intervals (T_0_-T_1_) and (T_1_-T_2_) in the intervention only and waiting-list control group and after the (T_2_-T_3_) follow up. This process enables a comparison of the rate of change in the caregivers who did not receive the intervention compared to the caregivers who received the intervention (T_0_-T_2_), and it provides insight into whether the potential effects on the outcome variables will be sustained by evaluating the rate of change from the 16-week follow up to the 42-week follow up (T_2_-T_3,_ intervention group only). Furthermore, LMM accounts for the fact that the data are correlated through nesting in individuals. Potential missing values are handled efficiently under the missing at random (MAR) assumption, using maximum likelihood estimates for the missing observations; hence, it is suitable for intention-to-treat analysis. Therefore, variables known to predict missing values will be included in the LMM analyses [38]. Intervals will be entered as categorical variables, using three dummies. The best model fit of the models with random intercept (at the participant level) and with random intercept and random slope (at interval level) will be compared with likelihood ratio tests. All tests will be two-tailed, with an alpha level of 0.05.

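### The primary 16-week ANCOVA does not fix the baseline score of the outcome as a covariate; adjustment follows an undefined "if necessary" rule, which costs precision and leaves the primary model dependent on the data

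*Protocol article*

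**What the plan says.** All of this is in the Protocol article.

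- **Endpoint and data.** Under Methods/design, the 16-week assessment (T2) is the primary endpoint for comparing the groups. Baseline questionnaires precede the intervention: "Self-reported data will be collected pre-intervention".
- **Baseline tests.** Under Primary and secondary outcome measures (Statistical analysis), t tests and chi-squared tests are planned on baseline data: "To investigate whether randomisation was successful, potential differences in the baseline characteristics" of the two groups will be examined this way.
- **Primary model.** The same section assigns the first hypothesis to an ANCOVA with the T2 outcome as dependent variable and group as the between-subject variable, run separately for each outcome. On covariates it says only: "Potential baseline differences between the treatment arms will be included as covariates, if necessary".
- **Second model.** A linear mixed model over T0 to T3 is then described for change over the whole study period.
- **Error rate and size.** "All tests will be two-tailed, with an alpha level of 0.05". The Sample size section gives "alpha 0.05 and power 80" percent, "with a mean effect size of 0.5", and a target of 51 analysable caregivers per group.

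**The concern.** A covariate earns its place in a randomised comparison because it predicts the outcome, not because the arms happen to differ on it. The T0 score of the same questionnaire is usually the best predictor available, and here it is already collected. Under the rule as written it enters only when someone judges a baseline difference to need it. Otherwise the model is a plain comparison of T2 means.

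Two things are at stake, for both primary outcomes and for every secondary outcome:

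1. **Precision.** Variance that T0 would explain stays in the error term.
2. **Prespecification.** With no criterion for necessity, the primary model can be settled only after the data are seen.

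The baseline tests do not help. Allocation is computer-generated and controlled by an independent researcher (Randomisation section), so baseline differences arise by chance. A P value therefore does not show whether randomisation worked. It is also a poor way to choose covariates: a non-significant difference in a strong predictor can matter, and a significant one in a non-predictor does not.

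**Working it through.** **Inputs from the article:** standardised effect d = 0.5; two-sided alpha 0.05; n = 51 per group analysable; 122 enrolled, so 61 per group.

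**Assumed input:** the correlation r between the T0 and T2 scores. The article gives none, so I use 0.3 to 0.7.

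**1. The plan's own figure.** The article says "we aim to include 102 primary caregivers (51 participants per group" for 80% power.
- A two-sided unadjusted comparison of two means needs 64 per group by the t distribution (63 by the normal approximation), not 51.
- A one-sided t test gives 51.
- A two-sided ANCOVA gives 51 only at an unstated r of about 0.44 (normal approximation).
- The stated basis is "using repeated measures and interaction within and between variables". With f = 0.25, two to four measures and r from 0 to 0.7, it gives total sizes of 16 to 66, not 102.

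So the stated size does not show which model was meant. I take 51 per group as given and ask what each analysis delivers.

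**2. Power of the T2 comparison.** Including T0 multiplies the residual SD by √(1 − r²). The noncentrality is d/√(1 − r²) × √(n/2), with 2n − 2 degrees of freedom unadjusted and 2n − 3 adjusted.

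Unadjusted: 0.5 × √25.5 = 2.525, power **70.6%**.

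| r | noncentrality | power with T0 | gain (points) |
|---|---|---|---|
| 0.3 | 2.525/0.954 = 2.647 | 74.6% | 4.0 |
| 0.4 | 2.525/0.917 = 2.755 | 77.9% | 7.3 |
| 0.5 | 2.525/0.866 = 2.915 | 82.3% | 11.8 |
| 0.6 | 2.525/0.800 = 3.156 | 87.8% | 17.3 |
| 0.7 | 2.525/0.714 = 3.536 | 93.8% | 23.3 |

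If 20% of the 122 are lost, 122 × 0.8 = 97.6 remain, about 49 per group. Power is then 68.8% unadjusted and 72.8% to 92.9% adjusted over the same range of r.

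**3. Does the conditional rule recover the gain?** Simulation with 51 per group and 8,000 runs per setting. The rule is read as adjusting for T0 only if its baseline t test has p < 0.05.

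| r | never adjust | conditional | always adjust |
|---|---|---|---|
| 0.3 | 70.9% | 71.2% | 74.0% |
| 0.5 | 70.4% | 71.4% | 81.9% |
| 0.7 | 69.8% | 71.9% | 93.5% |

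The conditional rule recovers almost none of the gain. With no true effect it rejected in 4.6%, 4.8% and 3.7% of runs, so type I error is not inflated.

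**4. Chance imbalance that can pass unadjusted.** With 61 per group, the largest baseline difference that is still non-significant is t(0.975, 120) × √(2/61) = 1.980 × 0.181 = 0.36 SD. At r = 0.5 it carries 0.5 × 0.36 = 0.18 SD into the unadjusted estimate, which is 0.18/0.5 = 36% of the planned effect. This is the edge of the range. A difference of one standard error (0.18 SD) would carry about 0.09 SD.

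**The case against.** **The word ANCOVA implies a baseline covariate.** It leaves some room for that intention. But the article goes on to list the model terms without one and makes covariates conditional. If T0 adjustment was intended, the text misstates it and needs the same edit.

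**The article does not link the tests to covariate choice.** This stands. Their stated purpose is to check the randomisation, and no threshold is given for necessity. A reader might infer that p < 0.05 formally triggers adjustment; the text makes that natural, since no other means of finding baseline differences is described, but it does not say it. The simulation and the 0.36 SD figure depend on that reading. The absence of a fixed T0 term does not.

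**The mixed model uses T0.** This also stands, so a reader who infers that the whole plan discards baseline goes too far. That model compares rates of change, including between the arms over T0 to T2. But the hypothesis about T2 differences is given to the ANCOVA, so the mixed model does not cure the defect.

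**The trial remains valid.** Agreed. Over repeated randomisations the unadjusted comparison is unbiased and keeps its type I error. The 0.18 SD is an upper bound on what one unlucky allocation could leave in the estimate under the test-driven reading at r = 0.5. It is neither typical nor systematic.

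**An analysis plan may settle this.** It may, but the protocol does not merely stay silent: it states a rule, and the rule is a poor one.

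**Conclusion.** The point holds in this form: the primary T2 ANCOVA does not fix the baseline value of the outcome as a covariate, and the rule for adding covariates is undefined and apparently driven by observed imbalance.

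The size depends on a correlation that the article does not give. At 51 per group, always adjusting gains about 4 points of power if r = 0.3, 12 if r = 0.5 and 23 if r = 0.7. It would be tempting to state a loss of 12 points as fact, but that figure belongs to r = 0.5 alone. The calculations also treat the scores as roughly normal with a linear T0–T2 relation, which is an approximation for a 0-to-7 score such as the SSCQ.

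The consequence is lost precision and a primary model open to choice after the data are seen, not a biased trial. It is best classed as a free improvement.

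**What to change.** Replace the conditional covariate sentence with:

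*Each T2 ANCOVA includes the T0 value of that outcome as a covariate, regardless of observed imbalance; no covariate is selected by baseline significance tests.*

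Describe baseline characteristics by arm in place of testing them.

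The cost is one sentence and one degree of freedom per model. No new data or participants are needed, because the T0 scores are already collected. The change should be dated and made before outcome data are examined by arm.

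### The 16-week group effect is analysed by two non-equivalent models at 0.05; the T2 ANCOVA adjusts for baseline only conditionally, and the mixed model is not labelled supportive

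*Protocol article*

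**What the plan says.** All of this is in the protocol article. Methods/design makes the 16-week assessment (T2) the primary endpoint for comparing the groups. Under Statistical analysis, Primary and secondary outcome measures, the first hypothesis is tied to an ANCOVA: "The outcomes assessed at the T_2_ follow up will be included in the model as dependent variables and groups as between-subject variables". On baseline, the rule is "Potential baseline differences between the treatment arms will be included as covariates, if necessary". The outcome's own baseline score is not named as a covariate, and no criterion for necessity is given.

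The same section then introduces an LMM to test change in the primary and secondary outcomes across the whole study. "The LMM will estimate the fixed effects of the regression slopes representing the changes during the intervals" T0-T1 and T1-T2, and the T2-T3 follow-up. Its stated uses are a "comparison of the rate of change in the caregivers who did not receive the intervention" with treated caregivers over T0-T2, and a look at whether effects last from T2 to T3 in the intervention group. The section closes with "All tests will be two-tailed, with an alpha level of 0.05". It does not say how the T0-T2 result of the LMM ranks beside the ANCOVA.

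Under Sample size, the target of 51 per group was derived "using repeated measures and interaction within and between variables with a mean effect size of 0.5", at alpha 0.05 and 80% power.

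**The concern.** Over T0-T2, both models address the same question in the same groups on the same outcomes, but they are not one analysis run twice. A T2 comparison without the baseline score leaves any chance baseline imbalance in the estimate. A comparison of change subtracts all of it. An ANCOVA with the baseline score removes the part that predicts T2. The planned ANCOVA moves between the first and third of these according to what the baseline data look like.

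Two things are at stake. One is conflicting answers about the same effect, with the weight of the LMM result left unstated. The other is power, because the conditional rule usually leaves out the covariate that would sharpen the T2 comparison.

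**Working it through.** **Inputs.** From the article: 51 per group, effect 0.5 SD, two-sided 0.05. Assumed: baseline-T2 correlation ρ, which the article does not give (0.5 to 0.7 for power and disagreement, 0.3 to 0.8 for error); complete data; normal scores with equal SD; and 'if necessary' read as adding the outcome's baseline score when its imbalance has p < 0.05.

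**The plan's own figure.** At 0.5 SD and 80% power, a two-group t test needs 51 per group one-sided (power 80.6%) and 64 two-sided. A two-sided unadjusted comparison with 51 per group has 71% power. A two-sided test reaches 80% with 51 per group only if the repeated measures are used: ρ of about 0.59 for change scores, or about 0.43 for ANCOVA with the baseline score. So at two-sided 0.05 the stated power is not available from an unadjusted T2 comparison.

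**The estimators.** Let D0 and D2 be the group differences at T0 and T2, in SD units, with n = 51.

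- Unadjusted T2: D2, variance 2/n.
- LMM contrast over T0-T2 with complete data: D2 − D0, variance 4(1 − ρ)/n.
- ANCOVA with the baseline score: approximately D2 − ρD0, variance 2(1 − ρ²)/n.

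The standard error of D0 is √(2/51) = 0.198 SD, about 40% of the assumed effect. The correlation of the unadjusted T2 test with the change test is √((1 − ρ)/2), which is 0.50 at ρ = 0.5. For the baseline-adjusted test it is √((1 + ρ)/2), which is 0.87 at ρ = 0.5.

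**Power and disagreement at a true effect of 0.5 SD.** Simulation, 40,000 trials per setting. Disagreement means that exactly one of the T2 test and the change test is significant.

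| ρ | Power, conditional | Power, always adjusted | Disagreement, conditional | Disagreement, always adjusted |
|---|---|---|---|---|
| 0.5 | 71.3% | 81.7% | 27.1% | 16.0% |
| 0.6 | 72.0% | 87.4% | 25.9% | 11.2% |
| 0.7 | 72.3% | 93.7% | 26.2% | 5.9% |

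As a check on the adjusted power, Φ(0.5/√(2(1 − ρ²)/51) − 1.96) gives 83%, 88% and 94%. The conditional rule costs 81.7 − 71.3 = 10 points at ρ = 0.5 and 93.7 − 72.3 = 21 points at ρ = 0.7.

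**False positives with no effect, ρ from 0.3 to 0.8.** Probability that at least one of the two tests is significant, by form of the T2 test:

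- Unadjusted: 8.8 to 9.5% (bivariate normal calculation).
- Conditional: about 7.4 to 8.7% across simulation runs.
- Baseline score always included: 7.8 to 6.5% (bivariate normal calculation).

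Two independent tests would give 1 − 0.95² = 9.75%. The conditional T2 test on its own rejects in about 3 to 5% of null trials.

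**The case against.** The strongest reply is that the article does assign roles. T2 is the primary endpoint, the first hypothesis belongs to the ANCOVA, and the LMM is introduced for change over the whole study and for durability. Nowhere does the article say that success on either model counts, and a fuller ranking of models is commonly left to a statistical analysis plan. This largely stands. A reader might infer that the plan runs at about 9% error per outcome, or that nothing guides the choice between the models. The article supports neither. The 9% figure needs an unadjusted T2 test, which is not the planned conditional ANCOVA, and it also needs a rule that either model may carry the claim.

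Nor should one infer an error of 17 to 18% across the two primary outcomes. Two independent outcomes tested once each already give 9.75%, which is a separate matter from having two models. An argument from low power of the separate interval slopes also fails: the T0-T2 comparison and the ANCOVA both remain, and the power of each slope depends on how the effect accrues and on correlations that the article does not state.

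It can also be said that the word ANCOVA implies a baseline covariate. If the outcome's baseline score is always meant, the right-hand figures in the table apply and most of the problem goes. But the text makes baseline adjustment conditional and does not name that score. That is a stated choice, not a detail left for later.

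**Conclusion.** The point holds as a fault in how the analysis is fixed, not as a demonstrated inflation of type I error. If the ANCOVA alone decides, error per outcome is at most about 5%. The range of 6.5 to 9.5% applies only if a positive result on either model were claimed as efficacy.

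What does not depend on that reading is the cost of conditional adjustment. When the planned effect is real, about one trial in four gives conflicting answers from the two models, and the T2 test has some 10 to 21 points less power than it would with the baseline score always included. These sizes rest on ρ of 0.5 to 0.7, complete data and the p < 0.05 reading of 'if necessary'. With missing data the two models would differ further, since the ANCOVA uses list-wise deletion or multiple imputation and the LMM uses likelihood under missing at random. That effect is not quantified here.

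**What to change.** Make three changes of wording in the statistical analysis section:

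1. Always include the outcome's own baseline score as a covariate in the T2 analysis, whatever the baseline comparison shows.
2. State that this baseline-adjusted group contrast at T2 is the single efficacy test for each primary outcome.
3. Label the LMM comparison over T0-T2, the interval slopes and the T2-T3 change as supportive or descriptive.

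The ANCOVA can stay; replacing it with a mixed model is not needed to cure this. The baseline scores are already collected and the software is unchanged. The one small cost is giving up the option to claim efficacy from the LMM.

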## Background

In the upcoming years dementia will become more visible in our society. Not only due to the growing number of people with dementia (PwD), but also because care increasingly occurs at home. The limited available professional workforce and the high economic costs of dementia care place pressure on informal caregivers and on future dementia care providers [1]. The progressive nature of dementia poses stress and physical and emotional health challenges to informal caregivers [2]. There is no available cure for dementia, therefore, caregiver support interventions particularly focus on the maintenance of quality of life and social engagement [3]. Previous studies have shown that psychosocial caregiver interventions have a moderate effect on caregiver health outcomes [4]. Furthermore, caregivers do not always use available services because of the prevailing stigma and experienced threshold associated with asking for support [5, 6]. Therefore, it will become important to develop cost-effective, accessible and innovative caregiver support methods. The Internet might provide a new arena for support because worldwide Internet usage and computer literacy are rapidly growing [7].

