### Procedure

The primary caregivers in the intervention and control groups will be assessed at four time points: the baseline assessment (T_0_), after 8 weeks (T_1_), after 16 weeks (T_2_), and after 42 weeks (T_3_) (i.e., 6 months after T_2_). The waiting-list control group will be invited to start using Inlife after 16 weeks (i.e., following the completion of the T_2_ assessment). At the time of the 42-week follow-up assessment (T_3_), both groups will be exposed to Inlife. Table 2 shows the enrolment and assessment procedures. All data are collected using self-reported measurements that are completed online through a custom, secure and confidential questionnaire system. All primary caregivers will receive a personal link through which they can complete the questionnaires. The participants will have approximately 2 weeks to complete each measurement. If a measurement is incomplete after the first invitation, the participants will receive an automatic reminder email. If the measurements are still incomplete, the researcher will call the participant to request completion of the measurement. Only the involved research staff has access to the trial data. The trial results will be disseminated in publications.

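### The week 16 to week 42 slope in the intervention arm alone can describe maintenance of scores under continued access, but not whether a between-arm effect is sustained

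*Protocol article*

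**What the plan says.** Methods/design makes week 16 the point of comparison: "The 16-week follow-up assessment serves as a primary endpoint to compare group effects". It adds that "a long-term follow-up measurement is scheduled for 42 weeks" after baseline.

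The same section and Procedure describe what happens in between. "The waiting-list control group will be invited to start using Inlife after 16 weeks", while "caregivers in the intervention group are free to continue using the platform". Procedure states the consequence for T3: by then "both groups will be exposed to Inlife".

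The statistical analysis section fits a linear mixed model to both arms over the whole study. It compares the arms over T0-T2 and then says that "it provides insight into whether the potential effects on the outcome variables will be sustained by evaluating the rate of change" from T2 to T3, with the restriction "intervention group only" in brackets. The protocol gives no margin, reference trend or assumed untreated course against which that slope is to be judged.

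**The concern.** The quantity of interest changes within one sentence. Up to T2 an effect is a randomised difference between Inlife and waiting list. From T2 its persistence is to be seen in the change of one arm. Those are different quantities unless caregivers without Inlife would have stayed level from week 16 to week 42, and the protocol gives no ground for assuming that. Its Background points the other way: "The progressive nature of dementia poses stress and physical and emotional health challenges to informal caregivers".

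Continued use adds a second ambiguity. The intervention arm keeps access, so stable scores could reflect a lasting benefit of the first 16 weeks, ongoing use, or both.

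What is at stake is the 42-week statement in the trial report. As planned, an uncontrolled before-after change would be presented as evidence on the durability of a randomised effect.

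**Working it through.** The protocol attaches no figure to the T2-T3 analysis, so there is none to reproduce. The check has two parts.

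**Inputs from the protocol**
- Planning effect 0.5 (Sample size), read here as 0.5 SD of the outcome.
- 51 per group for analysis and 122 enrolled with 20% loss (Sample size). 122 / 2 = 61 per arm, and 61 × 0.8 = 48.8, about 49. So n is taken as 49 to 51.
- T2 at week 16 and T3 at week 42, so 42 − 16 = 26 weeks.
- Both arms have access to Inlife after T2 (Methods/design, Control condition, Procedure).

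**Assumptions, not in the protocol**
- Correlation r between T2 and T3 scores of 0.3 to 0.7, equal SDs at the two visits, and a simple paired change as an approximation to the model's slope.
- g, the untreated drift from T2 to T3 in SD units, and k, the share of the T2 effect retained at T3. Both are unknown.

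**1. What the slope identifies**

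Expected change in the intervention arm = g + 0.5(k − 1).

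| Drift g | Share kept k | Change in arm (SD) |
|---|---|---|
| 0 | 1 (all kept) | 0 + 0 = 0.00 |
| +0.5 | 0 (all lost) | 0.5 − 0.5 = 0.00 |
| −0.5 | 1 (all kept) | −0.5 + 0 = −0.50 |
| 0 | 0 (all lost) | 0 − 0.5 = −0.50 |

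A flat slope and a slope of −0.50 SD each fit both extremes. These drifts are chosen to show the ambiguity, not as forecasts. A milder case shows the same: −0.25 SD is full retention with g = −0.25, half lost with g = 0, or all lost with g = +0.25. One observed number cannot determine two unknowns, and no arm supplies g after week 16.

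**2. Precision, even if drift were zero**

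SE of the change = sqrt(2(1 − r) / n); 95% half-width = 1.96 × SE.

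| r | n | SE (SD) | Half-width (SD) | Half-width / 0.5 |
|---|---|---|---|---|
| 0.3 | 49 | sqrt(1.4/49) = 0.169 | 0.331 | 66% |
| 0.3 | 51 | sqrt(1.4/51) = 0.166 | 0.325 | 65% |
| 0.5 | 49 | sqrt(1.0/49) = 0.143 | 0.280 | 56% |
| 0.5 | 51 | sqrt(1.0/51) = 0.140 | 0.274 | 55% |
| 0.7 | 49 | sqrt(0.6/49) = 0.111 | 0.217 | 43% |
| 0.7 | 51 | sqrt(0.6/51) = 0.108 | 0.213 | 43% |

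Power to detect a fall of 0.25 SD (half the planning effect), two-sided 5%, n = 51, is Φ(0.25/SE − 1.96): 33% at r = 0.3, 43% at r = 0.5 and 64% at r = 0.7.

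**The case against.** The case for leaving the text alone has real substance.

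- **The wording is hedged and open.** The protocol speaks of insight, states the restriction to one arm, and discloses that both groups have Inlife at T3. This stands, and it limits the weight of the point. It does not change what the slope is said to give insight into.
- **No rule equates non-significance with persistence.** A reader might infer that a non-significant slope will be reported as a sustained effect, since a two-tailed 5% level is the only criterion given. The protocol does not say so. The precision figures show what such a reading would be worth; they do not show that it is planned.
- **Control data are not discarded.** A reader might infer that the plan drops the control arm after T2. The mixed model takes both arms over the total study period, and only the maintenance reading is confined to one arm.
- **Other biases can be overstated.** Regression to the mean has no evident source, because nobody is selected on T2 scores and eligibility sets no score threshold. Attrition is partly handled by maximum likelihood under missing at random, with predictors of missingness in the model. Drift and continued use carry the argument.
- **The control arm shows an untreated course over T0-T2.** It does, and it could inform an assumption about drift. But it covers an earlier 16 weeks, not the following 26, and carrying it forward cannot be tested.
- **The gap comes from the design.** True: no model restores an untreated comparator after crossover. That argues for restricting the claim, not for keeping it.
- **This is detail for the analysis plan.** It would be if the protocol were silent. Here it names an analysis and ties it to an inference that the analysis cannot support.

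**Conclusion.** The point holds in a limited form. The T2-T3 slope in the intervention arm can describe whether scores are maintained under continued access. It cannot separate a retained effect from background drift or ongoing use, and this follows from the protocol's own text without any numerical assumption.

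The precision argument does rest on assumptions. With r from 0.3 to 0.7 and n of 49 to 51, the half-width is about 0.21 to 0.33 SD, 43% to 66% of the planning effect. A reader might infer that a slope near zero would always be compatible with losing more than half of that effect. This fails at r = 0.7, where the half-width is 43%, and the protocol states no correlation.

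Two further readings are not supported. The primary result is not in doubt, because T2 is already the primary endpoint and precedes the controls' access. Nor would a T3 comparison of the arms settle persistence: no difference there fits controls catching up to a fully kept effect and equally fits loss in both arms.

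The point should be corrected, but it concerns a secondary, long-term question.

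**What to change.** In the statistical analysis section:

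1. Replace the inference about sustained effects with maintenance of scores under continued access. Report the T2-T3 change in the intervention arm as an estimate with a 95% confidence interval, labelled descriptive and uncontrolled.
2. Report the control arm's T2-T3 change beside it, noting that it is measured after Inlife was offered and is not an untreated reference.
3. If the arms are compared at T3, label the contrast early versus delayed start (about 42 versus 26 weeks of access). State that it is a randomised comparison but not Inlife versus no Inlife, and that it does not by itself show persistence.
4. State that effectiveness claims rest on T2.

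The cost is a few lines of wording and, if wanted, one extra contrast. T3 is already collected in both arms, so no new data or participants are needed. The downside is a more modest long-term claim.
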